### Statistical analysis

Data of patients who receive at least one treatment will enter the primary intention-to-treat (ITT) analysis. The secondary per-protocol analysis (PP) will consider data of patients who participated in at least 80% (24/30) of the intended stimulation sessions.

Missing values will be imputed using multiple imputation approaches. The multiple imputation approach is used in the primary analysis. Complete case and last observation carried forward analysis will serve as sensitivity analysis. We expect to use monotone data imputation (missings caused by dropouts but not intermediate missing values in the time course) [47]. Thus natural predictors in the imputation model are preceding measurements of the outcome variable including baseline. Additionally, potential predictors as listed in the description of exploratory analyses will be included. Reproducibility will be ensured by the use of random seeds and variation due to the sampling process in the imputation will be reduced by a large number of imputation samples (*n* = 1000). The primary analysis will use a logistic regression model with MADRS ≤ 50% of baseline (yes/no) as dichotomous outcome, treatment arm as factor, baseline MADRS (continuous scale) and study center as covariate (factor). The goodness of fit for the logistic regression analysis will be inspected by use of the Hosmer–Lemeshow test. No interim analysis or planned subgroup analyses will be performed.

#### Secondary analyses

In a linear model, the outcome MADRS will be analysed as continuous variable. Covariates will be the same as in the primary analysis. Key secondary endpoints will be tested similarly with linear and logistic regression models. Additionally, mixed models will be applied to model the entire course of the primary and secondary outcomes during the study.

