## Design and methods

This prospective study is designed as a multicenter, randomized, double-blind, placebo-controlled clinical trial and aims to demonstrate the superiority of bilateral theta burst stimulation compared to a placebo condition (i.e. sham TBS) over a 6 weeks treatment period (30 sessions, five per week, daily from Monday to Friday) in patients with MDD.

Altogether 236 patients will be randomly assigned (1:1 ratio) to the two parallel treatment arms. Patients will receive either active combined iTBS/cTBS, or sham iTBS/sham cTBS, respectively. In each session, cTBS will be applied to the right and iTBS to the left dlPFC successively. Active and sham stimulation will be applied as add-on treatment to stable ongoing standard care (psychopharmacological and/or psychotherapeutic therapy). Study assessment with the observer- and self-ratings will be conducted for screening and baseline, after the 2nd, 4th, and 6th week of treatment, and during the follow-up period at two time points (1 and 3 months after end of treatment period).

Two associated satellite projects, entitled ‘MRI-based prediction of TBS-treatment efficacy in MDD’, and ‘Multiomics-analysis based prediction of TBS-treatment efficacy in MDD’ focus on the identification of potential treatment predictors.

This detailed description of the study protocol follows the recommendations of the SPIRIT statement [40].

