#### Secondary outcome measures

The considered secondary endpoints are (1) remission rate after treatment period which is defined as MADRS score ≤ 10 (2) comparison (active vs. sham) of raw score reduction of MADRS, HDRS-17, CGI, BDI-II, WHO-5, and WPAI during (a) treatment phase and (b) during follow-up (1 month and 3 months after end of treatment) compared to baseline for each time point; (3) number and severity of adverse events in both treatment arms and (4) deterioration rate after treatment which is defined as an increase of MADRS score of 25% compared to baseline.

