### Sample size calculation

In an own pilot study (*n* = 32) we found 9/16 (56%) responders (MADRS ≤ 50% of baseline) in the verum group and 4/16 (25%) responders in the sham group [28]. In a second pilot study (*n* = 60) of another group [29] response rates (HDRS-17 ≤ 50% of baseline) were 66.7% vs. 13.3% after 2 weeks treatment and 4/15 (27%) vs. 1/15 (7%) after week 14. In the third pilot study (*n* = 56) [30] response rates (HDRS-17 ≤ 50% of baseline) were 55% (bilateral TBS) and 30% (sham TBS), 7 weeks after initiation of a 3 weeks treatment. In a recent large (total *n* = 385) clinical trial [18] comparing iTBS (*n* = 193) with 10 Hz rTMS (*n* = 192) the outcome criterion of HDRS-17 ≤ 50% of baseline was achieved by 49% of patients treated with iTBS. Based on these studies, we conservatively assume a response rate of 49% vs. 30% (combined bilateral TBS vs. sham TBS) using the criterion MADRS reduction of at least 50% compared to baseline. This leads to a sample size of 103 subjects per group (Chi-square test, alpha = 0.05 two-sided, beta = 0.2), totally 206 evaluable subjects. As we will recruit in seven centers we increase the sample size by *n* = 6 to compensate for degrees of freedom in a stratified analysis which leads to 212 patients. The analysis will be done on the full set of patients except for those refusing consent during the study or not receiving at least one treatment. We expect a low dropout rate and therefore, we increase the sample size by 24 subjects to adjust for 10% dropouts, which leads to a total n of 236 patients.

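### Read literally, the plan adjusts the five non-MADRS secondary scales for baseline MADRS and names no own-baseline term, which costs some precision (minor, free to fix)

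*Protocol article*

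**What the plan says.** All references are to the protocol article.

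- **Statistical analysis.** The primary logistic model for response has "treatment arm as factor, baseline MADRS (continuous scale) and study center as covariate (factor"). No other baseline score is named for any analysis model.
- **Secondary analyses.** The section opens with a linear model for MADRS as a continuous outcome and continues: "Covariates will be the same as in the primary analysis. Key secondary endpoints will be tested similarly with linear and logistic regression models". It then adds mixed models for the whole course, without stating their covariates.
- **Secondary outcome measures.** The scale outcomes are a "comparison (active vs. sham) of raw score reduction of MADRS, HDRS-17, CGI, BDI-II, WHO-5, and WPAI", each measured against baseline and at each time point. They are change scores, and five of the six scales are not MADRS.
- **Table 2.** CGI, BDI-II, WHO-5 and WPAI are rated at the baseline visit. HDRS-17 is rated before treatment at screening only.

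**The concern.** An analyst who follows the text would fit the change in, say, BDI-II on arm, centre and baseline MADRS. Using a change score does not make the own-baseline term unnecessary. Subtraction fixes the baseline coefficient at 1, whereas the efficient value is the regression slope of follow-up on baseline. Where that slope is below 1, the change score still depends on the starting value: patients who start worse tend to show larger reductions. Baseline MADRS absorbs only the part of this that it shares with the scale.

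At stake is the precision of the self-rated, global, well-being and work outcomes, together with some sensitivity of their estimates to chance differences between arms at the start.

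**Working it through.** **The plan's own figure.** The inputs are "we conservatively assume a response rate of 49% vs. 30" per cent and "Chi-square test, alpha = 0.05 two-sided, beta = 0.2". With pooled variance, the mean rate is 0.395:

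n = [1.960·√(2·0.395·0.605) + 0.842·√(0.49·0.51 + 0.30·0.70)]² / 0.19² = (1.355 + 0.571)² / 0.0361 ≈ 103 per arm.

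Then 206 + 6 = 212, and 212/0.9 = 235.6, which rounds up to 236. The sample size reproduces and does not depend on this point. The article states no power for the secondary scales.

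**Inputs for this point.** There are 106 evaluable patients per arm (212/2). The following are assumptions, because the documents give no values:
- r, the correlation of a scale's own baseline with its follow-up;
- q, the correlation of its baseline with baseline MADRS;
- k, the follow-up SD divided by the baseline SD;
- baseline MADRS predicts follow-up only through the scale's own baseline.

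**Residual variance of the change score, in units of the baseline variance.**
- Adjusted for own baseline: k²(1 − r²)
- Adjusted for baseline MADRS: k² + 1 − 2rk − q²(1 − rk)²
- Difference: (1 − rk)²(1 − q²)

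With k = 1 the first two become 1 − r² and 2(1 − r) − q²(1 − r)².

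| k | r | q | Own baseline | Baseline MADRS | Ratio | Cut |
|---|---|---|---|---|---|---|
| 1 | 0.3 | 0.4 | 0.910 | 1.322 | 0.69 | 31% |
| 1 | 0.3 | 0.7 | 0.910 | 1.160 | 0.78 | 22% |
| 1 | 0.4 | 0.5 | 0.840 | 1.110 | 0.76 | 24% |
| 1 | 0.6 | 0.4 | 0.640 | 0.774 | 0.83 | 17% |
| 1 | 0.6 | 0.7 | 0.640 | 0.722 | 0.89 | 11% |
| 1.5 | 0.3 | 0.5 | 2.048 | 2.274 | 0.90 | 10% |
| 1.5 | 0.4 | 0.5 | 1.890 | 2.010 | 0.94 | 6% |
| 1.5 | 0.5 | 0.5 | 1.688 | 1.734 | 0.97 | 3% |

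**Power, r = 0.4, q = 0.5.** With k = 1 and an effect of 0.35 SD, the standard errors are √(2·0.840/106) = 0.126 and √(2·1.110/106) = 0.145. The ratios of effect to standard error are 2.78 and 2.42, so power is about 79% with own baseline and 68% with baseline MADRS. With k = 1.5 the loss is much smaller. An effect that has 80% power with own baseline has a ratio of 2.802·√(1.890/2.010) = 2.717 with baseline MADRS, or about 78% power.

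**Chance imbalance, k = 1.** Suppose the arms differ by d SD at baseline on the scale analysed. The expected MADRS difference is then qd, and the MADRS coefficient on the reduction is q(1 − r). The expected shift left in the estimate is (1 − r)d − q(1 − r)·qd = (1 − r)(1 − q²)d. At r = q = 0.5 this is 0.5·0.75·d = 0.375d.

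The root-mean-square shift from the part of the imbalance that MADRS does not explain is (1 − r)·√(1 − q²)·√(2/106) = 0.5·0.866·0.137 = 0.059 SD. The standard error is 0.133 SD with baseline MADRS and 0.119 SD with own baseline, and 0.119² + 0.059² ≈ 0.133². The imbalance and the lost precision are therefore one loss, counted once.

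**The case against.** The strongest reply is that the article never says that the other scales are adjusted for baseline MADRS. The covariate sentence comes directly after the continuous MADRS model, where baseline MADRS is the own baseline. The next sentence says only that the key secondary endpoints are tested *similarly*, which could mean own baseline plus centre. The imputation model uses earlier values of the outcome being imputed, which shows that the authors think in outcome-specific terms. *Key* is undefined, so not all five scales need be covered. A condensed article may also leave a covariate list for each scale to a fuller document.

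Much of this stands. A reader might infer a settled decision to use baseline MADRS for every scale, but the text supports this only as its literal reading. What remains is that the article does fix a covariate set, carries it forward and names no alternative.

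Two further inferences go too far:
- **That a chance baseline imbalance stays in the estimate in full, or biases it.** MADRS adjustment removes a fraction q² of the expected shift (16-49% for q = 0.4-0.7), and randomisation keeps the estimate unbiased on average.
- **That 11-31% is the expected loss.** That range needs equal SDs. The entry requirement of at least 18 points on HDRS-17 trims the spread at the start, while follow-up scores are not trimmed. For the depression scales a wider follow-up SD, and so the smaller loss, is at least as plausible.

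The mixed models may also handle baseline differently, but the article does not say.

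**Conclusion.** The point holds as a minor one. On the literal reading, the linear models for HDRS-17, CGI, BDI-II, WHO-5 and WPAI omit the most useful baseline covariate and use a weaker substitute. The cost is residual variance that own-baseline adjustment would cut by about 11-31% with equal SDs (r 0.3-0.6, q 0.4-0.7), or by about 3-10% with a follow-up SD 1.5 times the baseline SD (r 0.3-0.5, q 0.5). All of these correlations and SD ratios are assumed. If baseline MADRS carried information on follow-up beyond the scale's own baseline, the gap would narrow.

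Type I error, the primary analysis, the sample size and the MADRS-based secondary outcomes (score, remission, deterioration) are untouched.

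**What to change.** In Secondary analyses, state that each continuous secondary outcome is analysed in a linear model with arm, centre and the pre-treatment value of the same scale. For HDRS-17 this is the screening value, the only one collected. Keep baseline MADRS as the baseline covariate for MADRS-based outcomes, and use the same baseline term in the mixed models.

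With the own baseline in the model, the treatment estimate is the same whether the outcome is written as the change or as the follow-up score, so the outcome definition need not change.

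The cost is one sentence. The values are already collected, and one continuous covariate replaces another, so no patients, visits or degrees of freedom are added. If own-baseline adjustment was always intended, the sentence records that before unblinding.

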#### Exploratory analyses

Potential prognostic factors (disease duration, severity, degree of treatment resistance, age, sex) will be included in the multiple regression models with main effects and interactions (moderator effects) with treatment arm.

#### Descriptive analyses

They will include absolute and percentage frequencies for categorical variables, means, medians, standard deviations, quartiles and ranges for quantitative variables and medians, quartiles, and ranges for ordinal variables. Percentages will be estimated using an exact confidence interval for proportions based on the binomial distribution. The differences between subgroups will be tested using the Chi-square test (proportions), or the *t*-test for independent samples (normally distributed measures). Safety will be assessed by frequency tabulations, line listings, and exact 95% confidence intervals. All statistical analysis will be done using the software SPSS and R in the newest release.

### Documentation, monitoring and data management

With the exception of the data of the two satellite projects, all relevant data will be entered into a paper case report file (paperCRF) by responsible study team members. After monitoring, copies of the CRFs will be transferred to the central data management institution (see below). Each study center must store the original CRFs and other study-specific data for a minimum of 10 years.

The Center of Cinical Studies, University Tübingen (ZKS Tübingen) will monitor the implementation of the study with regard to correctness and Good Clinical Practice (GCP) conformity, which includes the review of the CRF entries in all trial sites. The main aims of the monitoring visits include the verification of the informed consent documents, existence of the patients, inclusion- and exclusion criteria, completeness and accuracy of entries on the CRFs (i.e. primary endpoint data). In each study center, the monitoring timeline includes an initiation visit, three visits per year and center during the recruitment period as well as a close-out visit after the complete documentation of the last patient/after clarification of queries by data management and/or monitoring.

The IKEaB is responsible for data management and will use Koordobas as a data management system, to which only authorized staff has password-protected access. After completion of monitoring of the CRF entries, the monitor will send a copy of the CRF to the data management. To ensure high data quality, IKEaB will implement double data entry by two different employees. Possible inconsistencies will be clarified by subsequent data reconciliation. At the same time, the data will be checked for completeness and plausibility. In case of queries, the data management sends a data query report to the respective center where responsible staff members will check original CRFs/source data for inconsistencies. After completion of data clearance, there will be a blind data review to determine the analysis population (intention-to-treat population, per-protocol population, and safety population).

### Safety aspects and Data Safety Monitoring Board

The exclusion criteria of this study include the currently valid contraindications for rTMS treatment [4]. In addition, a safety check (i.e. skin examination) is performed before each TBS session and immediately afterwards. Possible adverse events (AEs) or serious adverse events (SAEs) will be documented during the six-week treatment phase in accordance with the guidelines of GCP and will be followed up until complete recovery and/or the patient’s status is stable. AEs and SAEs must be reported to the monitoring facility and Data Safety Monitoring Board whose three members are independent and not affiliated with participating centers.

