**Fig. 1 Fig1:**
[figure not shown]
Trial flow

**Table 2 Tab2:** Study flow chart

	Study period												
	Pre-Treatment		Treatment									Follow-up	
Week	0		1	2		3	4		5	6		10	18
Visit	Screening	Baseline	V1-V5	V6-V10	V10	V11-V15	V16-V20	V20	V21-V25	V26-V30	V30	V31	V32
Informed consent	X												
Sociodemography	X												
Pregnancy test^1^	X												
Physical/neurological examination	X												
Concomitant treatment^2^	X	X			X			X			X	X	X
SCID-5-PD	X												
ATHF-SF	X												
MADRS (item 10 only)	X												
HDRS-17	X				X			X			X	X	X
Randomization	X												
MADRS (complete)		X			X			X			X	X	X
BDI-II		X			X			X			X	X	X
CGI		X			X			X			X	X	X
WHO-5		X									X	X	X
WPAI		X									X		X
THINC-it^®^ (test of cognition)		X									X		X
CTQ		X											
EHI		X											
MRI^3^		X											
Genetics^3^		X									X		X
Determination of resting motor threshold^4^		X											
Active iTBS/cTBS sham iTBS/cTBS													
Safety check													

^1^Pregnancy test is only necessary for women in child-bearing age; if a blood sample is taken as part of the clinical routine, it is advisable to check a possible pregnancy with a blood test. Otherwise, a urine test can be used to avoid unnecessary risks

^2^Concomitant medication and/or any type of psychotherapy will be documented for each patient for his/her entire participation period

^3^MRI and Genetics are not part of the standard protocol but belong to two satellite projects

^4^Alternatively, the threshold can also be determined directly before the first stimulation, i.e. in visit 1

Study treatment will start on Monday within the week after completion of the baseline session (deviations in case of holidays are possible). During the treatment phase, each patient will receive a total of 30 TBS sessions over a period of 6 consecutive weeks (one session daily from Monday to Friday).

Ratings will take place at the end of the 2nd, 4th, and 6th weeks after the respective stimulation session.

Within the follow-up period two visits are scheduled, 1 month and 3 months after the end of treatment. Patient participation in the study will end with last follow-up.

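### New adverse events and SAEs are recorded only in the six treatment weeks, so SAEs that begin between week 7 and the last visit at week 18 are not recorded as SAEs, and the safety endpoint becomes on-treatment without saying so

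*Protocol article*

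**What the plan says.** Under Safety aspects and Data Safety Monitoring Board, the protocol article says: "Possible adverse events (AEs) or serious adverse events (SAEs) will be documented during the six-week treatment phase". Events so documented "will be followed up until complete recovery" or until the patient is stable. AEs and SAEs go to the monitoring facility and to an independent three-member board.

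Under Study timeline, "each patient will receive a total of 30 TBS sessions over a period of 6 consecutive weeks". After that, "Within the follow-up period two visits are scheduled, 1 month and 3 months after the end of treatment"; Table 2 places these visits (V31, V32) at weeks 10 and 18. "Patient participation in the study will end with last follow-up".

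Under Secondary outcome measures, item (3) is the "number and severity of adverse events in both treatment arms", with no time window. Item (2) compares the efficacy scales in the treatment phase and also "during follow-up (1 month and 3 months after end of treatment) compared to baseline for each time point". A footnote to Table 2 says that concomitant medication and psychotherapy "will be documented for each patient for his/her entire participation period". Under Blinding, patients, staff and the analysing statistician stay blinded until the analysis is complete.

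**The concern.** The recording rule closes at the end of week 6, and nothing else in the article provides for an event that first occurs later. The follow-up clause applies to events already documented. The board reporting sentence has no time limit of its own, but an event that is never documented cannot be reported.

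The patients have a moderate or severe episode with at least one failed adequate antidepressant treatment in that episode (Table 1). Admission for depression or suicidal behaviour in the three months after treatment is plausible and could differ by arm. Rating scales at two visits describe patients who attend; they do not register an admission or an attempt as a serious event.

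Two things are at stake. The board's information on SAEs would stop at week 6 while the blinded trial continues to week 18. And the published safety comparison would be on-treatment only, beside efficacy results to week 18, in a trial whose abstract looks to support a well-tolerated treatment.

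**Working it through.** **Inputs.** Recording window: 6 weeks (Safety aspects). Treatment: 30 sessions in 6 weeks (Study timeline). Last visit: week 18 (Table 2). Patients: 236, allocated 1:1, so 118 per arm.

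**The plan's own figure.** The article gives no figure for safety follow-up time. The patient number used below does reproduce: 2 × 103 = 206; 206 + 6 = 212; 212 / 0.9 = 235.6, rounded up to 236.

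**Calendar time outside the window.**
- From start of treatment to last visit: 18 weeks. Outside the window: 18 − 6 = 12 weeks.
- Share: 12 / 18 = 66.7%.
- With three months taken as a quarter year, 52.18 / 4 = 13.05 weeks: 13.05 / (6 + 13.05) = 68.5%.

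**Patient-weeks, upper bounds that ignore dropout.**
- Inside the window: 236 × 6 = 1,416.
- Outside: 236 × 12 = 2,832.
- Total: 236 × 18 = 4,248.

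**Exposure outside the window.** All 30 sessions fall in weeks 1 to 6, so 0 of 30 sessions are uncovered.

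**What could go unrecorded.** The article gives no rate of serious events after treatment. As an assumption, let p be the proportion of one arm with a new SAE in weeks 7 to 18, with independent patients and no dropout. Expected number per arm = 118 × p; chance of at least one = 1 − (1 − p)^118.

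| p (assumed) | Expected per arm | Chance of at least one |
|---|---|---|
| 1% | 1.2 | 69% |
| 2% | 2.4 | 91% |
| 5% | 5.9 | over 99% |

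Even at 1%, an SAE in a given arm is more likely than not.

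**What is collected in weeks 7 to 18.**
- Recorded at V31 and V32 (Table 2): complete MADRS including item 10, HDRS-17, BDI-II, CGI, concomitant treatment.
- Recorded throughout: medication and psychotherapy, with changes after treatment registered at follow-up (Concomitant treatment).
- Continued: follow-up of events that began in treatment.
- Not provided for: a new event classified as an AE or SAE, and its report to the board.

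The Safety check row of Table 2 came through without marks and is not used either way. The text ties that check to each stimulation session.

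**The case against.** The strongest defence is that an on-treatment safety window is a legitimate choice. Every session lies inside it, with a check before and after each, so acute stimulation effects are covered. After week 6 the medication-constancy rule lapses, so an arm difference in later events would mix the effect of TBS with changed co-treatment. The article also condenses a fuller protocol that may hold longer SAE rules.

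Much of this stands, and it rules out several stronger readings that a reader might infer:

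- **That two thirds of the safety information is lost.** The 67% is calendar time. No event rate is given, and the weeks that carry all the exposure are covered.
- **That the article contradicts itself.** Item (2) of the secondary outcomes names follow-up explicitly; item (3) promises no adverse event comparison there. An on-treatment reading fits both sections.
- **That delayed worsening would appear only as a MADRS score.** Three other scales and the treatment record are also taken at both follow-up visits.
- **That a patient absent because of a serious event would simply be missing.** The Discussion plans a comparison of dropouts with completers. Follow-up absence cannot touch the primary endpoint, which is assessed at the end of treatment.
- **That motor threshold determination before visit 1 distorts the safety comparison.** It is done in the same way in both arms, with a separate coil, and may take place at visit 1 itself.

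What the defence does not supply is a route for recording a new SAE after week 6. The article states a closed window, so this is a rule as written and not a detail left out. Difficulty of attribution is a reason to tabulate the periods separately and interpret follow-up events with care; it is not a reason to leave SAEs unrecorded.

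**Conclusion.** The point holds as a weak design choice that should be improved. As written, new SAEs that begin in weeks 7 to 18 are not recorded as SAEs and have no stated path to the monitoring board, and the secondary safety endpoint is on-treatment only without being labelled so. The extent is 12 of 18 weeks of calendar time, or at most 2,832 of 4,248 patient-weeks before dropout. The number of events lost cannot be derived from the article; the figures for 1% to 5% rest on an assumed rate.

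The primary endpoint, sample size and efficacy analyses are not affected. The conclusion assumes that the stated window is the operative rule. If the full protocol already records SAEs to the last visit, the article's sentence needs correcting and the data gap disappears.

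**What to change.** - Extend recording and board reporting of at least SAEs, and of AEs judged related to TBS, through V32, by adding an adverse event page at V31 and V32.
- Tabulate treatment-phase and follow-up events separately by arm, with a note that co-treatment may change after week 6.
- In the definition of the secondary safety endpoint, label the treatment-phase comparison as on-treatment.
- Optional and minor: open the window at motor threshold determination. This does not change the arm comparison.

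Cost: two case report form pages per patient at visits that already exist, short changes to the protocol text, and some extra SAE reporting in follow-up. No new visits and no change in sample size. If the sponsor prefers to keep the six-week window, the least change is to say openly that the safety endpoint is on-treatment only; that cures the labelling but leaves later SAEs unrecorded.
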